### Data collection

#### Quantitative data

Effectiveness outcomes will originate from the data sources shown in table 2. Data collected by nurses or data operators from the EHR include age, gender, duration of diabetes, use of insulin, parental history of diabetes, other complications of diabetes including diabetic kidney disease, cardiovascular complications, and diabetic foot, random blood sugar results, urine dipstick test for albuminuria and blood pressure record. Other study-specific data collected by nurses or data operators on the day of screening include education status, occupation and income categories, and previous history of DR, cataract surgery or any other ocular history. In addition, they will measure body mass index, waist circumference and complete a lifestyle questionnaire on smoking, diet, physical activity, EQ-5D vision bolt-on.^24^ The EQ-5D vision bolt-on will be used to calculate the quality adjusted life-years and utility value for economic analysis. EQ-5D alone does not capture visual acuity deficits.^25^ The EQ-5D vision bolt-on asks patients to rate their health across six dimensions: mobility, self-care, usual activities, pain/discomfort, anxiety/depression and vision. Each dimension is scored in five levels: no problems, slight problems, moderate problems, severe problems and extreme problems. A recent study provided utility values based on EQ-5D vision bolt-on. The mapping was done in a clinical trial cohort with macular oedema in central retinal vein occlusion.^26^

In the reading centre, the data collection will include the grade of retinopathy in both eyes, presence of cataract and gradability of the retinal images. Data collected on referred patients will include numbers with ungradable images due to cataract, treatment options offered for DR and review appointment.

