### Statistical analyses

We will create a complete case data set of the cross-sectional survey for use in the analyses of effectiveness and assess the potential impact of missing data using sensitivity analysis incorporating a range of optimistic and pessimistic scenarios for the impact of missing data. We will model two outcomes that we hypothesised would be influenced by the intervention: (1) uptake of DR screening (primary outcome) and (2) numbers of patients referred for STDR as a result of screening. We will use bivariate logistic regression models to assess crude associations between sociodemographic factors such as age, gender, education, income and living arrangements, and other clinical data with DR and STDR and use fractional polynomials to account for the form of continuous covariates to predict uptake of DR screening. Factors associated with a p<0.25 will be candidates for inclusion in the multivariable logistic regression models. We will test interactions among identified main effects to capture improvement in model prediction assessed by reduced residual variance-based statistics. To account for the staggered entry into the study, we will add a variable indicating the month of entry of each FHCs into the programme (eg, 1. if the FHC join in the first month of the programme, 2. if in the second month and so on). A non-significant coefficient for this variable will suggest the staggered approach had no effect and a significant coefficient will allow the effect to be quantified for each FHC. In our final adjusted model, we will consider associations with a p<0.05 as statistically significant. Adequacy of model discrimination and calibration will be assessed using receiver operating characteristic curves. The validation of the telemedicine will be reported as the agreement (kappa statistics) between screen positive patients graded by the graders at the reading centre versus the DR grade as recorded by the ophthalmologists in secondary care centres. A kappa coefficient of 0.6 or higher was prespecified to indicate validity.

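### ROC curves are named as the check on calibration, but they measure discrimination only and cannot detect miscalibration in any of the planned models

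*Protocol article*

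**What the plan says.** The Statistical analyses section of the protocol article names one check of model adequacy: "Adequacy of model discrimination and calibration will be assessed using receiver operating characteristic curves". It names no other calibration measure.

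The models to be checked are built as follows.

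- Two outcomes are to be modelled: uptake of screening (the primary outcome) and "numbers of patients referred for STDR as a result of screening".
- Crude logistic associations are planned for sociodemographic factors, and the sentence goes on: "and other clinical data with DR and STDR and use fractional polynomials to account for the form of continuous covariates to predict uptake". The fractional polynomials are thus tied to the uptake model.
- The entry rule for the adjusted models reads: "Factors associated with a p<0.25 will be candidates for inclusion in the multivariable logistic regression models".
- On interactions, the stated purpose and yardstick are "to capture improvement in model prediction assessed by reduced residual variance-based statistics".
- The significance rule reads: "In our final adjusted model, we will consider associations with a p<0.05 as statistically significant".

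The Sample size section derives 1131 patients for the uptake proportion. Among people with diabetes it expects 8% with diabetic retinopathy (DR), 3% with STDR and about 20% needing referral. The Target population section invites everyone with diabetes on the registers of 16 FHCs.

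**The concern.** Discrimination and calibration are separate properties. Discrimination asks whether patients with the event receive higher predicted risks than those without. Calibration asks whether predicted risks agree with observed frequencies. A ROC curve is built from ranks alone, so it answers only the first question.

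This is a stated method that cannot do its job, not a detail left open. An analysis plan that followed the sentence would carry the error forward. Prediction of uptake is an aim given in the same section, so calibration matters to the plan's own purpose. At stake is a report that calls a model well calibrated on evidence that could not have shown otherwise.

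A second question is whether an STDR model, if fitted, would have enough events for the variables on offer.

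**Working it through.** **1. ROC curve and calibration.** Let the predicted log-odds be L. Replacing L by L + a (shift), or stretching L about a fixed point by a factor b > 0, keeps the order of all patients. Sensitivity and specificity along the curve depend only on that order, so the ROC curve and AUC cannot change. The predicted risks, 1/(1 + exp(−L)), do change.

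Numerical check: 20,000 simulated patients with true log-odds −3.8 + x, where x is standard normal. The event rate is 3.3%, close to the plan's STDR figure.

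| Predictions used | AUC | Mean predicted risk | Observed risk | Calibration slope |
|---|---|---|---|---|
| Correct | 0.744 | 3.3% | 3.3% | 0.96 |
| Log-odds shifted by 1.5 | 0.744 | 12.2% | 3.3% | 0.96 |
| Log-odds stretched by 2 about −3.8 | 0.744 | 7.6% | 3.3% | 0.48 |

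The second row overstates risk 3.7-fold (12.2/3.3). The third has half the slope of the first. The ROC curve is identical in all three.

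**2. Why optimism correction is preferable.** In an unpenalised logistic model with an intercept, fitted by maximum likelihood, the calibration intercept and slope are exactly 0 and 1 in the fitting data by construction. There, only the calibration plot is informative. The intercept and slope need resampling or new data.

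Two illustrations use n = 1131, 3% events, a p<0.25 screen and then a multivariable fit.

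- 25 pure-noise factors, 400 data sets: about 6 factors pass the screen. Mean AUC is 0.70 in the fitting data and 0.50 in new patients, where the calibration slope is about 0.
- 22 factors, three of them real (odds ratio 1.5 per SD), 200 data sets: AUC is about 0.75 in the fitting data and 0.64 in new patients, with a calibration slope of about 0.5.

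The number and strength of the factors are assumptions, so these figures show direction, not a forecast.

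**3. The plan's sample size.** 377 × 3 = 1131. The mean cluster size is 1131/16 = 70.7, so the ICC is (3 − 1)/(70.7 − 1) = 0.029, matching the stated value of about 0.03. The 377 is approximately reproduced under unstated assumptions (expected proportion 50%, margin ±5 points, 95% confidence): a population of 40 000 gives 381, within about 1%.

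**4. Events available at 1131 screened.**

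- STDR: 0.03 × 1131 = 33.9
- DR: 0.08 × 1131 = 90.5
- Referral for any reason: 0.20 × 1131 = 226

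The Quantitative data section lists the variables collected, starting with "age, gender, duration of diabetes, use of insulin, parental history of diabetes, other complications of diabetes including diabetic kidney disease". Together with living arrangements and month of FHC entry from the Statistical analyses section, they come to about 25 single terms. If 20 to 25 were offered to an STDR model, there would be 33.9/25 = 1.4 to 33.9/20 = 1.7 events per candidate, before category indicators or interactions.

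**5. Range for STDR if more are screened.**

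| Screened | STDR events (3%) | Events per candidate at 25 |
|---|---|---|
| 1131 | 34 | 1.4 |
| 5,000 | 150 | 6 |
| 10,000 | 300 | 12 |
| 40 000 | 1,200 | 48 |

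**The case against.** The strongest reply is that little depends on the sentence. The primary effectiveness outcome is a proportion, factor associations are declared by p<0.05 in the adjusted model, and no risk score is to be deployed. All of that stands. Correcting the calibration method would change neither the primary result nor the list of significant factors, which limits the weight of the point. It does not rescue the sentence, because the plan sets out to judge calibration and names a tool that cannot do so.

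A reader might infer more than the document supports:

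- **That the checks could never expose a poor model.** A ROC curve can show poor discrimination. What it cannot show is miscalibration or, if computed only in the fitting data, optimism.
- **That any interaction would be accepted.** Raw residual deviance cannot rise when a term is added, but the text says interactions will be tested and leaves the statistic unnamed. A deviance (likelihood-ratio) test fits that wording and does reject terms.
- **That validation will use only the fitting data.** The article names no resampling or other data, but it does not exclude them, and an article commonly leaves this to the full plan.
- **That the STDR model is sure to have 34 events for over 20 factors with polynomials on top.** The 1131 is not a cap on the number screened. The variable list describes data collection and is not a candidate list. The fractional polynomials are tied to uptake. The second modelled outcome is referral for STDR, and if all referrals counted there would be about 226 events at 1131 screened. In the other direction, fewer than 34 would be available if the 1131 includes people not screened, with ungradable images or with incomplete data.

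**Conclusion.** The point holds for calibration. The method named for it cannot detect miscalibration in any planned model, whatever the number screened. This follows from the definition of the ROC curve and needs no assumption about the data. In the example, a 3.7-fold overstatement of risk left the AUC unchanged at 0.744. It is a correctable error that should be put right, but it does not threaten the primary outcome.

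The STDR event count is secondary and conditional. It matters only if a multivariable STDR model is fitted and the number screened stays near 1131. By an assumed yardstick of 10 events per candidate, 20 to 25 candidates would need about 6,700 (200/0.03) to 8,300 (250/0.03) screened. The primary uptake model is not limited by STDR prevalence.

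**What to change.** Reword the sentence so that ROC curves and AUC assess discrimination only. Assess calibration with a calibration plot, intercept and slope for each model. Preferably correct all of these, and the AUC, for optimism with a bootstrap that repeats the p<0.25 selection in each resample and respects clustering by FHC.

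If a multivariable STDR model is fitted, limit its number of terms to what the events obtained can support. A short list fixed in advance is one way to do this.

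The cost is a little more analysis work and no new data. The corrected AUC may be lower than the uncorrected one. With only 16 FHCs a cluster bootstrap will be coarse, which should be said when the results are reported.

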### Setting

Target sites for implementation of DR screening and treatment in Thiruvananthapuram will include 16 FHCs for DR screening which represents the primary care centres where patients are screened for all complications of diabetes. The retinal images, captured by the trained, resident nursing staff will be sent to a newly developed reading centre at the Regional Institute of Ophthalmology, a tertiary care centre, where newly accredited graders will grade the images. Patients with screen-positive images will be referred to three secondary care hospitals (district hospitals). Severe cases that require complex interventions will be referred to the tertiary care centre, the tertiary for specialist management of DR.

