### Evidence-based clinical intervention

The new DR care pathway is the intervention and is shown in figure 1. The pathway will span primary, secondary and tertiary care. The components of the pathway are:

DR screening of patients with diabetes registered in the non-communicable diseases register at FHCs (primary care). The retinal images will be graded remotely at the reading centre at the tertiary centre.Prompt referral for timely treatment of STDR to secondary care and tertiary centres depending on the severity of the DR.Treatment of patients with sight threatening DR (at secondary and tertiary care).

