	Conduct educational meetings	Hold meetings targeting different stakeholder groups (ophthalmologists, family health centres staff, ASHAs, patients). Three educational meetings are planned by the UK team to meet with the providers in the family health centres settings to share knowledge and educate providers about the DR care pathway and its integration into their clinical practice.
	Achieve accreditation for graders of retinal images	Train and certify the optometrists in the Reading Centre in the tertiary centre to obtain accreditation as graders using the online international Test and Training for retinal graders.
	Conduct ongoing training	Nurses and doctors in the family health centres will receive on-going training on DR, pupil dilatation and capture of retinal images using low-cost smartphone retinal cameras.^29 30^
	Create a learning collaborative	The Health Secretary of State will foster a collaborative learning environment to improve implementation of the DR care pathway.
	Use train-the-trainer strategies	The UK team will first train a batch of family health centres nurses to capture retinal images and then some will be trained to train the rest of the nurses. The same cascading pathway will apply to laser training.
	Work with educational institutions	Moorfields Eye Hospital staff will provide the necessary guidance and share knowledge on UK diabetic retinopathy screening pathway.
	Make training dynamic	All staff involved will receive continual online or face-to-face training.
	Increase demand	The ASHAs will be trained to increase public awareness of this pathway in their house-to-house health visits.
	Provide ongoing consultation	The UK team from Moorfields Eye Hospital will provide ongoing consultation to support implementation of DR care pathway.
Infrastructure	Centralise technical assistance	The project manager and the EHR team will provide central assistance focused on implementation issues. The telemedicine project will link the patient’s retinal images to EHR and transfer through a secure cloud to the tertiary centre, where the images will be graded for their DR status in a newly developed reading centre, with the results fed back to the family health centres.^31^
	Change physical structure and equipment	Evaluate current configuration of family health centres consulting rooms to allow suitable furniture for cameras and adapt illumination to capture retinal photographs.

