Adoption	Uptake of DR care pathway at primary, secondary and tertiary care. Uptake of training by staff. Uptake of screening programme by patients. Adoption of DR care pathway by the Government of Kerala for state-wide implementation.	*Assessment:* Proportion of staff at primary, secondary and tertiary care willing to integrate DR care pathway in their workload. *Data source:* Family health centres data and staff interviews. *Assessment:* Demand training sessions; attendance rates at training sessions. *Data source:* Number of training sessions and attendance registers at training sessions. *Assessment:* Increase in proportions of patient screened over 12 months. *Data source:* EHR and study database. *Assessment:* A policy paper by the Government of Kerala for state-wide adoption of the DR care pathway as part of diabetes care for all patients. *Data source:* A detailed scale-up plan will be developed for each district based on the clinical and cost-effectiveness data from this study to inform policy.
Appropriateness	Appropriateness of family health centres for DR screening. Appropriateness of the complex DR care pathway across primary and secondary care. Appropriateness of referrals to secondary care.	*Assessment:* Qualitative data on barriers and facilitators of the delivery of screening and treatment in secondary care. *Data sources:* Interview of staff at family health centres and secondary care, patient telephone survey on pathway from FHCs to secondary care. *Assessment:* False positive referrals from data collection at secondary care. *Data sources:* Study database; data from patient telephone survey.
Cost	Costs to the Government of Kerala and societal costs of the DR screening programme and subsequent treatment.	*Assessment:* Costs of the DR screening and treatment costs in total and per person, including the costs of staff training and cameras (suitably annuitised), staff costs and travel costs of patients. *Data sources:* Data collected in the study baseline and data from other services in India and from the literature.
Feasibility	Screening rate per family health centres. Barriers to monthly screening uptake.	*Assessment:* Monthly increase in numbers of FHCs added to the programme. *Data source:*Interview and monthly report from project manager on facilitators and barriers on each part of the pathway.

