Fidelity	Degree of the DR care pathway implementation. Validation of the DR grading within the telemedicine pathway. Delivery of training and the impact on the DR care pathway.	*Assessment:* Fidelity evaluation in 16 family health centres using a path-process analysis of the screening to identify the common screening pathway across centres. *Data source:* The path-process analysis will be based on detailed time-event logs of 70 patients from the 16 family health centres; a telephone follow-up of referred patients to evaluate uptake of referrals. *Assessment:* Validation of the DR grading will be assessed by the agreement of the DR grade reported by the optometrists at the reading centre in the tertiary centre and those reported by the ophthalmologists in the secondary care centres. *Data sources:* DR grading of referred patients obtained from the reading centre vs secondary care. *Assessment:* Increase in numbers of trained staff per month. *Data sources:* Staff interviews, structured observations and review of facility records. The proportions of doctors trained on laser delivery; data quality on the database; increase in non-communicable diseases registration following start of programme due to training of ASHA workers on diabetes and DR; increase in numbers of patients treated for STDR following training.
Penetration	Increase patient awareness of diabetes and DR and uptake of the DR screening pathway in patients with diabetes.	*Assessment:* Increase uptake of DR screening by patients registered in non-communicable diseases registers. *Data sources:* from non-communicable diseases register and EHR.
Sustainability	Policy makers to prepare policy on up-scale and sustainability plan for DR pathway. Integration of DR pathway in weekly activities in FHCs	*Assessment:* Availability of a policy paper from Government of Kerala on state-wide scale up of the DR care pathway. This will be considered a success of the programme. *Data sources:* Scale up plan for other districts including plan to purchase retinal cameras and acceptance of guidelines and training material for state-wide roll out. *Assessment:* Integration of DR pathway in EHR. *Data source:* EHR records of DR screening as part of non-communicable diseases care pathway.

ASHA, accredited social health activists; DR, diabetic retinopathy; EHR, electronic health records; FHCs, family health centres; STDR, sight-threatening diabetic retinopathy.

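### The validity kappa takes the ophthalmologist's referral-visit grade as its reference, and nothing in the plan keeps that grade independent of the reading-centre grade

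*Protocol article*

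**What the plan says.** **The comparison.** The Statistical analyses section validates the telemedicine pathway by one measure: "agreement (kappa statistics) between screen positive patients graded by the graders at the reading centre versus the DR grade as recorded by the ophthalmologists". These are the ophthalmologists of the secondary care centres. The section then sets a limit: "A kappa coefficient of 0.6 or higher was prespecified to indicate validity". Table 3 (Outcomes, Fidelity) repeats the comparison as "agreement of the DR grade reported by the optometrists at the reading centre in the tertiary centre and those reported by the ophthalmologists", again those of secondary care, with the data source given as "DR grading of referred patients obtained from the reading centre vs secondary care".

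**How the patient reaches the second grader.** The Setting section states: "Patients with screen-positive images will be referred to three secondary care hospitals (district hospitals"). The Evidence-based clinical intervention section lists as a pathway component: "Prompt referral for timely treatment of STDR to secondary care and tertiary centres depending on the severity of the DR".

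**Where the reading-centre result goes.** Table 1 (Implementation strategies, Infrastructure) describes images linked to the electronic record and graded at the reading centre, "with the results fed back to the family health centres". Nothing says whether the secondary-care ophthalmologist sees the result or is masked to it.

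**Expected disagreement.** Table 3 (Appropriateness) takes as an assessment: "False positive referrals from data collection at secondary care".

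**The concern.** Kappa speaks to the validity of one grader only if the second grade is made independently. Here the second grade is the one recorded at a referral visit that exists because the first grade was positive. No separate validation reading is described. If the reading-centre grade is in view when the ophthalmologist records a grade, borderline disagreements may be settled in its favour, and the agreement would then partly reflect the referral information.

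The plan attaches a pass/fail label to this number. Agreement somewhat below 0.6 could be reported as valid, and a reader of the results could not tell whether that had happened.

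**Working it through.** **The plan's own figure.** The 0.6 limit comes with no expected kappa, sample size or derivation, so there is nothing to reproduce. The question is what anchoring does to a kappa judged against it.

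**1. Direction, in the patients the plan analyses.** Let Po be observed agreement, Pe chance agreement, and S the sum of squared reading-centre grade proportions. Let a share *a* of disagreements be resolved towards the reading-centre grade, uniformly across cells. Then

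- Po′ = Po + a(1 − Po)
- Pe′ = (1 − a)Pe + a·S, because the ophthalmologist's marginals move towards the reading centre's
- 1 − κ′ = (1 − a)(1 − Po) / [(1 − a)(1 − Pe) + a(1 − S)]

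Since a(1 − S) is not negative, 1 − κ′ cannot exceed (1 − Po)/(1 − Pe) = 1 − κ. So kappa rises for any *a* above 0, provided the reading centre uses more than one grade among these patients and some disagreement exists.

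**2. Size near the limit.** True kappa 0.50 and *a* of 20% or 25% are assumptions; the documents give neither.

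*Chance agreement unchanged (S = Pe):* κ′ = 1 − (1 − a)(1 − κ).

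- a = 20%: 1 − 0.80 × 0.50 = 0.60
- a = 25%: 1 − 0.75 × 0.50 = 0.625

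*Unequal marginals.* In screen-positives the reading centre cannot contribute a no-DR grade but the ophthalmologist can. Assume marginals (0, 0.6, 0.4) for the reading centre and (0.3, 0.4, 0.3) for the ophthalmologist.

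- Pe = 0 + 0.24 + 0.12 = 0.36; S = 0.36 + 0.16 = 0.52; Po = 0.36 + 0.50 × 0.64 = 0.68
- a = 20%: Po′ = 0.744, Pe′ = 0.288 + 0.104 = 0.392, κ′ = 0.352/0.608 = 0.58
- a = 25%: Po′ = 0.76, Pe′ = 0.27 + 0.13 = 0.40, κ′ = 0.36/0.60 = 0.60

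The range is about 0.58 to 0.63.

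**3. Size far below the limit.** Take three grades (no DR, DR that is not STDR, STDR) with prevalence 92/5/3%. This comes from the 8% DR and 3% STDR under Sample size, reading the 3% as part of the 8%. The error rates are assumed. Each cell gives the probabilities of being graded no DR / non-STDR DR / STDR.

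| Grader | True no DR | True non-STDR DR | True STDR |
|---|---|---|---|
| Ophthalmologist | .98/.019/.001 | .06/.88/.06 | .01/.09/.90 |
| Reading centre, good | .97/.027/.003 | .10/.82/.08 | .02/.10/.88 |
| Reading centre, middle | .95/.045/.005 | .15/.75/.10 | .03/.15/.82 |
| Reading centre, poor | .92/.07/.01 | .25/.60/.15 | .05/.25/.70 |

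The table below gives unweighted kappa with independent grades, then the anchoring needed to reach 0.6 in screen-positives, with chance agreement updated as in step 1.

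| Reading centre | All screened | Screen-positives only | Anchoring to reach 0.6 |
|---|---|---|---|
| Good | 0.647 | 0.353 | between 40% (0.56) and 50% (0.62) |
| Middle | 0.557 | 0.240 | about 60% (0.602) |
| Poor | 0.429 | 0.125 | about 70% (0.606) |

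Modest anchoring therefore matters when true kappa is just under 0.6. When it is far below, a pass needs heavy anchoring.

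**4. A separate effect in the other direction.** Step 3 also shows that restriction to screen-positives lowers kappa in all three settings. If the grade is reduced to DR yes/no, one grader is constant in this set and kappa is 0 whatever the grading quality.

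**The case against.** The strongest reply is that the article nowhere says the ophthalmologist sees the grade. Results go back to the family health centres. Referral shows selection on the reading-centre grade, which is different from knowledge of it. Everyone in the kappa was referred, so referral alone does not reveal which grade was given. False-positive referrals are an outcome, so the plan expects second grades that differ from the first. A condensed article may also leave masking to the full protocol.

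Much of this stands. A reader might infer that the ophthalmologist normally knows the grade, that grades are copied, and that kappa is inflated as a matter of fact. The documents support none of these. What remains is that the article fixes the reference as the grade recorded at the referral visit and labels 0.6 as validity. Recording that grade before the reading-centre grade is opened is a better method than the one stated, at little cost. If it is already done, the added field documents it.

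A second reply is that restriction to screen-positives lowers kappa, so good grading may fail 0.6. This is correct when the set is compared with all screened patients. It does not answer what anchoring does within the screen-positive set, where the limit is applied and where anchoring raises kappa (step 1).

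A third reply is that the constant-chance formula overstates the rise when marginals differ. In the example it does: 0.58 against 0.60 at 20%. The stated range allows for this.

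**Conclusion.** The concern holds in a limited form. The validity kappa rests on a referral-visit grade whose independence from the reading-centre grade nothing in the plan secures. Whether the ophthalmologist sees the reading-centre grade is not stated. If so, uniform anchoring of any amount raises kappa in the analysed set.

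The size, about 0.58 to 0.63 from a true 0.50, rests on an assumed true kappa, an assumed 20–25% share and the assumed marginals. It is an illustration and does not predict the result.

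Two further readings go too far. A reader might infer that a false pass would by itself carry the pathway to state-wide roll-out. Table 3 bases the scale-up plan on clinical and cost-effectiveness data, and no section makes roll-out depend on kappa. A reader might also infer that masking would make this kappa a full validation of the telemedicine grading. It would not: screen-negatives are not re-graded, so missed DR stays unseen, and the restriction to screen-positives may itself lower kappa.

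**What to change.** For the validation data, have the secondary-care ophthalmologist record the DR grade for each eye on the study form before opening the reading-centre grade and images, and add a field confirming that this was done. Compute the kappa judged against 0.6 in the patients with that confirmation, and report the others separately.

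Describe the result as agreement among referred patients. State that the fact of referral cannot be hidden from the ophthalmologist, that missed DR is not assessed, and that restriction to screen-positives may lower kappa.

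The cost is one form field, an instruction to the referral clinics and a short delay before the referral grade is opened. No extra examination or staff is needed.
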